### 2.7. Sample size

Based on the results of previous observational studies, the composite outcome of 90-day all-cause mortality or readmission for HF was approximately 25% among patients who received conventional therapy for acute heart failure (20, 21). We assumed that the composite rate of those who combined with YQFM in clinical practice is 18%. Setting a significance level of two-sided alpha level of 0.05 and 10% of the loss to follow-up, 1,200 patients would be enough to detect the composite outcome with 80% power.

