### 2.8. Statistical analysis

The baseline characteristic and observational data will be expressed as means ± standard deviation, medians, or percentages, and performed an independent t-test, Mann-Whitney U test, or Chi-square test/Fisher’s exact test, depending on the distribution.

Cox proportional-hazards regression models will be used to estimate the association between YQFM use and the primary outcome. An initial multivariable Cox regression model will include demographic factors, clinical factors, laboratory tests, and medications.

The primary analysis will use propensity-score matching methods to balance the differences in baseline variables between treatment cohorts. The individual propensities for receipt of YQFM treatment will be estimated with the use of a multivariable logistic regression model that include the same covariates as the Cox regression model. In the propensity-score matching analysis, the nearest-neighbor method will be applied to create a matched control sample. All variables will include in the propensity score model reflected knowledge available at baseline. Missing baseline variables will be handled by multiple imputation by chained equations using the other variables available. To verify the covariate balancing after the propensity score matching, the standardized mean difference (SMD) will be calculated with a threshold of 10% designated to indicate clinically meaningful imbalance (22). Kaplan-Meier curves and Cox models that use the propensity-score matching will be reported. A sensitivity analysis for unobserved confounding will be performed by using the Rosenbaum’s method to assess the robustness of findings due to hidden bias (23).

We will compare our findings with the AUGUST-AHF RCT study to determine whether the results, particularly the primary outcome, are compatible between the two. The proportion of patients who met the eligibility requirements for the AUGUST-AHF RCT study will be computed. Differences in baseline characteristics between those who met the RCT eligibility and those who did not will also be tested by the statistical methods described above.

We will perform an interim analysis when 33% of total patients (N = 400) have completed the 90-day follow-up. The interim analysis will be performed by independent statisticians, and we may adjust the course of the subsequent study or revise the study protocol based on the analysis results.

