All statistical analyses were performed with the R statistical package version 4.0.2 (R Foundation for Statistical Computing, https://www.R-project.org/). Furthermore, two-tailed p < 0.05 was considered statistically significant.

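### The interim at 400 patients allows open-ended, results-driven changes while the only test level is an unadjusted two-sided 0.05, so the 5% error rate and pre-specification are not guaranteed

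*Protocol article*

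**What the plan says.** All references are to the protocol article.

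- **Timing (section 2.8):** "We will perform an interim analysis when 33% of total patients (N = 400) have completed the 90-day follow-up". Ninety days is the window of the primary outcome, so primary outcome data exist for everyone in this look.
- **Consequence (section 2.8):** independent statisticians carry out the analysis, and then "we may adjust the course of the subsequent study or revise the study protocol based on the analysis results". No purpose, boundary, recipient or list of permitted changes accompanies this.
- **Test level (end of section 2.8):** "two-tailed p < 0.05 was considered statistically significant". No other level is given.
- **Sample size (section 2.7):** "Setting a significance level of two-sided alpha level of 0.05 and 10% of the loss to follow-up", the article concludes that "1,200 patients would be enough to detect the composite outcome with 80% power". The assumed 90-day event rates are 25% without and 18% with YQFM. No interim is mentioned.
- **Amendments (section 2.9):** modifications need ethics approval, and the amended protocol is published in a registry.
- **Not stated:** whether the interim compares exposed with non-exposed patients, and whether efficacy may be declared at it.

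**The concern.** An analysis of primary outcome data may lead to any change in the study or its protocol, and the final test is then read at the full 0.05. Two protections are lost.

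The first is the false-positive rate. A second chance to claim significance, or a design change driven by the observed effect, can push it above 5% unless the final level allows for it.

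The second is pre-specification. Section 2.8 names the covariates of the Cox and propensity models only by broad class, and section 2.3 sets the boundary between low and high exposure at 5 days on expert opinion. The clause would permit the covariates, the matching or that boundary to be revised once effects were known. In an observational comparison these choices can move the estimate, and no alpha adjustment repairs a model chosen by its result. Objective 2, the comparison with the AUGUST-AHF RCT, would suffer as well, because agreement with the trial means little if the cohort analysis could be reshaped along the way.

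Both the open-ended clause and the flat 0.05 are written in the article, so this is more than detail deferred to an analysis plan. An analysis plan could itself be revised under the same clause.

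**Working it through.** **Inputs.** From section 2.7: 25% versus 18%, two-sided alpha 0.05, 80% power, 10% loss to follow-up, N = 1,200. From section 2.8: interim at 400 patients. The exposure ratio is not stated; 1:1 is assumed.

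**1. The plan's own sample size.** Pooled-variance formula for two proportions, mean rate 0.215:

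n = [1.960·√(2·0.215·0.785) + 0.842·√(0.25·0.75 + 0.18·0.82)]² / 0.07² = 539.5, so 540 per group.

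2 × 540 = 1,080, and 1,080/0.9 = 1,200. The stated figure is reproduced exactly as a single-look design at 0.05, with power 80.04% at 540 per group. No interim allowance is built in.

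**2. Error rate if significance can be claimed at 0.05 at both looks.** The information fraction is t = 400/1,200 = 0.333, or 400/1,080 = 0.370 if counted against evaluable patients. Z₁ and Z₂ are bivariate normal with correlation √t:

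1 − P(|Z₁| < 1.96 and |Z₂| < 1.96) = 0.0883 at t = 0.333 and 0.0872 at t = 0.370.

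**3. Error rate if the remaining sample is resized on the interim effect, with an unadjusted final test.** For each interim value z₁, the stage-two size (f times that planned) is chosen to maximise the conditional error

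P(Z > (1.96√T − z₁√t)/√n₂) + P(Z < (−1.96√T − z₁√t)/√n₂), with n₂ = (1 − t)f and T = t + n₂,

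and the maximum is averaged over the null distribution of z₁. At t = 0.333:

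| Permitted size of the remaining sample | Worst-case two-sided error |
|---|---|
| as planned (f = 1) | 5.0% |
| 1 to 2 times planned | 5.7% |
| 0.5 to 2 times planned | 6.5% |
| 0 to 2 times planned | 10.1% |

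These are upper limits, not expected values. Changes to covariates, matching or exposure cut-off cannot be quantified this way.

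**4. Error rate if the interim is non-comparative or futility-only, with no other data-driven change.** At or below 5%.

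**5. What a comparative look could show.** With 200 versus 200, at the planned rates:

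SE = √(0.1875/200 + 0.1476/200) = 0.041, so the 95% interval is ±1.96 × 0.041 = ±0.080.

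That is ±8 points around a planned difference of 25 − 18 = 7 points. Power at 0.05 is 40%. Unequal exposure or loss through matching would make this worse.

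**6. Levels that hold 5% overall at t = 0.333.**

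| Rule | Interim p | Final p |
|---|---|---|
| Haybittle-Peto | 0.001 | 0.0495 |
| O'Brien-Fleming, classical | 0.0007 | 0.0497 |
| Lan-DeMets, O'Brien-Fleming type | 0.0002 | 0.0499 |
| Pocock | 0.0277 | 0.0277 |

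Power at 540 per group is 79.9% at a final level of 0.0495 and 80.0% at 0.0497, against 80.04% at 0.05.

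**The case against.** The strongest case on the other side has five parts.

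- **The interim may not be comparative.** Section 2.8 does not say that groups are compared or a hypothesis tested. A look at the overall event rate, share exposed or follow-up would be harmless, and 400 patients serve it adequately: at a pooled rate of 21.5%, the 95% half-width is 1.96·√(0.215·0.785/400), about 4 points. This stands. A comparison is a plausible inference from changes based on the results, but only an inference.
- **Looking does not by itself inflate error.** This also stands. A reader might infer that the true error rate is 8.8%, but that needs an efficacy claim at 0.05 to be possible at 400 patients, which the article does not say.
- **There are safeguards.** Independent statisticians do the analysis, and amendments are reviewed and published. These deserve credit for transparency, but they neither control error nor limit what reaches the team that acts on the results.
- **Interim details belong in the full protocol or analysis plan.** The absence of a boundary alone would be no finding. The defect here is the stated, unlimited permission combined with the stated flat level.
- **The effect on alpha is small next to confounding.** True of a Haybittle-Peto adjustment, which costs 0.0005, and the article itself concedes that bias is hard to remove. It does not answer the loss of pre-specification.

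A reader might also infer that a known interim effect would change who receives YQFM among the remaining 800 patients. The text establishes neither part. It does not say that treating physicians at the 50 hospitals see interim results. Nor does it pause recruitment: at even accrual (1,200 over 36 months, about 33 a month) roughly 100 more patients would be enrolled while the first 400 complete 90 days, leaving about 700.

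**Conclusion.** The point holds as a missing guarantee, not as a demonstrated inflation. The article permits unspecified changes after an analysis of primary outcome data and keeps an unadjusted 0.05, so nothing confines the study to the uses under which 5% is preserved.

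The error rate ranges from 5% or less (non-comparative or futility-only, nothing else changed) to about 8.8% (significance claimable at 0.05 at both looks), with a worst case of about 10% if the remaining sample may be resized anywhere from nothing to double. The figures assume the planned event rates where rates enter, normal test statistics, and information proportional to patients. They ignore confounding, which affects the true error rate separately.

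If the look is comparative, its precision (±8 points, 40% power, equal groups assumed) is a weak basis for redesign. Revising covariates, matching or the exposure cut-off after seeing effects would end pre-specification by an amount that cannot be computed. Once interim effects have been seen this cannot be undone, so the wording should be settled before the 400-patient data cut.

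**What to change.** Replace the open-ended clause in section 2.8 with one of the following, and state the interim's purpose, who sees the results and which changes it may trigger.

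1. **Non-comparative interim.** Limit it to pooled quantities: overall event rate, share exposed, missing data and covariate overlap. No effect estimate is released to investigators and no efficacy claim is made. The final level stays at 0.05.
2. **Effect test kept.** Use a Haybittle-Peto rule: p < 0.001 at the interim and a final two-sided level of about 0.0495. Comparative results go only to an independent group.

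Under either option, lock the exposure definition, covariate list, matching procedure and primary model before the interim data cut.

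**Cost.** Mostly wording. The final level drops by about 0.0005 only under option 2, and 1,200 patients still give about 80% power (79.9% at 540 per group). The team gives up the freedom to redesign the study on interim effects.

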Outcome	Primary outcome: 90-day all-cause mortality or HF readmission Secondary outcomes: 180-day all-cause death or HF readmission, length of hospital stay, 90-day cardiac-specific death, MACE, dyspnoea via VAS, dyspnoea via Likert 7-point scale, NYHA function class, MLHFQ scale, MMAS-8, heart rate at follow-up	Primary outcome: 90-day all-cause mortality or HF readmission Secondary outcomes: 180-day all-cause mortality or HF readmission rate, length of hospital stay, 90-day cardiac-specific death, MACE, dyspnoea via VAS score, dyspnoea via Likert 7-point scale, NYHA functional class, WHF, MLHFQ scale, intravenous diuretics, NT-proBNP
Follow-up	180 days	180 days
Study design	Cohort study	RCT

HF, heart failure; MACE, major cardiovascular adverse event; VAS, dyspnoea via visual analog scale; MLHFQ, minnesota living with heart failure quality of life; MMAS-8, morisky medication adherence scale; RCT, randomized controlled trial.

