#### 3.2.2. Study design rationale

In our study, we will apply a broader eligibility criterion and nearly the same outcome measures as the AUGUST-AHF RCT study (shown in Tables 1, 2). The study results will represent the long-term effectiveness of YQFM in a real-world setting.

Furthermore, we will compare the population and results of our study with the AUGUST-AHF RCT study. Complex patients with multimorbidity or a history of specific treatments, like heart transplantation, will be excluded from the AUGUST-AHF RCT investigation, raising concerns regarding the trial’s generalizability and the unknown benefit and risk of Yiqi Fumai Lyophilized Injection for this group. In our study, we specifically set up an assessment to determine whether patients are eligible for the AUGST-AHF RCT study. By comparing the populations of the two studies, we could determine the representativeness of the AUGUST-AHF RCT study populations to real-world patients and describe differences in the characteristics of patients who met the RCT eligibility criteria and those who did not participate in a real-world setting, something that is rarely mentioned in existing studies. Those who do not meet the AUGUST-AHF eligibility criteria will be analyzed separately to obtain efficacy in an underrepresented population.

Some studies have demonstrated that the outcomes of patients in clinical trials differ from those in real-world settings, with lower survival rates and a higher incidence of AEs (13, 14). The results of our study will be compared with AUGUST-AHF to verify whether this condition also exists in HF patients and to analyze its possible causes. The outcome measures are largely the same between the two studies, facilitating data comparability. Furthermore, differences in compliance between trial and non-trial patients have been cited as an important reason for differences in results (39). Thus, we will include compliance analysis as an important part of the study to explore the differences in compliance between patients in and out of clinical trials and their impact on clinical outcomes. The study outcomes will aid patients, physicians, and policymakers in selecting the optimal treatment options for all patient subgroups. The method could potentially serve as a model for utilizing RCT-validated data in routine clinical practice.

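### The only between-group methods stated for the non-primary data are unadjusted tests at two-tailed 0.05, so secondary comparisons of physician-chosen exposure would be confounded, with a moderate multiplicity risk on top

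*Protocol article*

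**What the plan says.** **Methods.** Section 2.8 opens with baseline and observational data, for which it says the study "performed an independent t-test, Mann-Whitney U test, or Chi-square test/Fisher’s exact test, depending on the distribution". It then links the Cox model by name to the primary outcome and introduces propensity-score matching as the method of the primary analysis. No adjusted method is stated for the continuous or ordinal secondary outcomes.

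**Threshold.** Section 2.8 closes with one rule that is not limited to any outcome: "two-tailed p < 0.05 was considered statistically significant".

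**Outcomes.** Table 1 lists ten secondary outcomes for the cohort, beginning "Secondary outcomes: 180-day all-cause death or HF readmission, length of hospital stay, 90-day cardiac-specific death, MACE, dyspnoea via VAS" and continuing with Likert dyspnoea, NYHA class, MLHFQ, MMAS-8 and heart rate. Section 2.4 lists nine, without heart rate. In Table 1 the 180-day composite and 90-day cardiac-specific death carry a time point, and length of stay is a single value. Table 2 schedules the other seven at several post-baseline times, and no analysis time is named for them. VAS, Likert, NYHA and MLHFQ also have a Day 0 value.

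**Exposure.** Section 2.3 describes an observational study with treatment at the physician's discretion. Groups are formed by whether YQFM was given during the stay.

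**The concern.** In a cohort where clinicians decide who is treated, a crude comparison mixes any drug effect with the reasons for treating. The plan recognises this for the primary analysis and uses matching there. If the scales and length of stay are compared with the only tests that section 2.8 states for them, that protection is lost. A difference in NYHA or MLHFQ at follow-up could simply reflect a difference at admission, although the admission value is on file.

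The single 0.05 threshold adds a smaller problem, because any of ten secondary outcomes could be called significant. At stake is how a secondary result is read beside a null primary. Section 3.2.2 states that "The study results will represent the long-term effectiveness of YQFM in a real-world setting" and expects the outcomes to guide treatment choices. A confounded or chance finding could then carry more weight than it should.

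**Working it through.** **1. The plan's own figure.** Section 2.7 gives 25% against 18%, two-sided alpha 0.05, 80% power and 10% loss. The allocation ratio is not stated, so I take 1:1. With pooled variance and mean rate 0.215:

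n = [1.960 × √(2 × 0.215 × 0.785) + 0.842 × √(0.25 × 0.75 + 0.18 × 0.82)]² / 0.07² = 539.5, so 540 per group. Then 2 × 540 = 1,080 and 1,080 / 0.90 = 1,200.

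The stated total is reproduced. It rests on the primary outcome alone, so changing the secondary analyses does not change it.

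**2. Which method covers which outcome.**

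| Data | Method stated in section 2.8 | Adjusted? |
|---|---|---|
| 90-day composite | Cox; propensity matching in the primary analysis | Yes |
| Other observational data | t, Mann-Whitney, chi-square or Fisher | No |

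The matched Kaplan-Meier and Cox results that section 2.8 promises could extend to the event-type secondaries (180-day composite, cardiac death, MACE). They do not suit VAS, Likert, NYHA or MLHFQ scores, and length of stay is not mentioned in connection with them.

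**3. Size of the confounding (illustration).** The documents give no imbalance figures. Take the plan's own 10% standardized-difference limit as the true imbalance in a baseline score, 540 per group and no drug effect. Let r be the assumed correlation between baseline and follow-up score. The crude test statistic is then shifted by 0.10 × r × √(540/2) = 1.643r. The chance of a significant result in the direction of the imbalance is Φ(1.643r − 1.960):

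- r = 0.3: Φ(−1.467) = 7%
- r = 0.5: Φ(−1.138) = 13%
- r = 0.8: Φ(−0.645) = 26%

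The nominal one-direction rate is 2.5%. Whether this favours or penalises YQFM depends on which group starts better. Before matching the imbalance could be larger or smaller than 10%.

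**4. Size of the multiplicity.** Ten outcomes (Table 1), one test each, no effect and no confounding:

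- Either direction, independent: 1 − 0.95¹⁰ = 40.1%
- Benefit direction only, independent: 1 − 0.975¹⁰ = 22.4%

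Simulation with equally correlated normal test statistics (200,000 draws; the correlations are assumed):

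| Correlation | Either direction | False benefit |
|---|---|---|
| 0.3 | 35% | 18% |
| 0.5 | 28% | 14% |
| 0.7 | 21% | 11% |

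With the nine outcomes of section 2.4, the independent figures are 1 − 0.95⁹ = 37.0% and 1 − 0.975⁹ = 20.4%.

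**The case against.** The strongest reply is that this is a condensed article, and a SAP that is not shown would normally settle multiplicity, the analysis visit for each scale and the models for secondary outcomes. The phrase about observational data could be read as descriptive, and section 3.2.2's companion discussion of bias speaks of propensity methods balancing the two cohorts without limiting this to one outcome. Much of this stands. The lack of a testing hierarchy or of named visits would not be a finding by itself. The article also never says outright that the secondary outcomes will be compared crudely. What remains is that section 2.8 does state methods, and the only ones it states for data outside the primary analysis are unadjusted and ignore the baseline score. Even inside a matched sample, a plain t or Mann-Whitney test would leave that score unused.

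Three stronger readings are tempting but not supported:

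- *A false YQFM benefit is likely.* With one test per outcome the chance is about 22% at most under independence or the positive correlations examined. Counting every scheduled post-baseline visit gives 42 tests and, if independent, 1 − 0.975⁴² = 65% for a false benefit. With assumed correlations of 0.8 within and 0.5 between outcomes it is 25%. Table 2 is a collection schedule, and nothing says that each visit will be tested.
- *No secondary outcome has a fixed time point.* Three of the ten do.
- *The long-term effectiveness statement rests on the 180-day secondary.* Section 3.2.2 does not say so. The Figure 1 legend uses similar long-term wording for the RCT, whose primary outcome is the same 90-day composite.

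**Conclusion.** The point holds as a weakness in the stated analysis of the secondary outcomes. It does not touch the primary outcome: there is one primary, and its type I error is not altered by tests of the secondaries.

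The main part is confounding. Its size cannot be derived from the documents, and the 7% to 26% above rests on an assumed imbalance, equal groups of 540 and assumed baseline-to-follow-up correlations. The multiplicity part is moderate: 11% to 22% for a false benefit over the correlations examined, against 2.5% for one test. Both parts depend on section 2.8 being applied as written. A fuller plan may already do better, in which case the article's text should say so.

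**What to change.** Revise section 2.8 as follows:

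- Analyse the secondary outcomes in the same propensity-matched sample, or with the same covariates as the Cox model.
- Include the baseline value as a covariate for VAS, Likert, NYHA and MLHFQ, using an ordinal model where the scale calls for it.
- Name one analysis time point, or one repeated-measures model, for each repeatedly measured scale.
- Keep the two-sided 0.05 claim for the matched 90-day composite. Report the other results as supportive estimates with 95% confidence intervals.
- Restrict the unadjusted tests to describing baseline characteristics.

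Also reconcile two places that define the family: heart rate is in Table 1 but not in section 2.4, and NYHA is scheduled at Days 0, 10 and 90 in Table 2 but confirmed at 30, 60, 90 and 180 days in section 2.6.2.

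The cost is a few sentences and slightly more analysis work, with no added patients. Fewer secondary results could be called significant.
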